### Secondary outcomes

#### Maternal outcomes will include

• length of labour (first, second and third stages),

• mode of birth (spontaneous vaginal birth, instrumental birth or caesarean section),

• perineal trauma (episiotomy, degree of laceration),

• incidence of maternal morbidity (e.g., postpartum haemorrhage, shoulder dystocia, chorionamnioitis),

• length of stay in hospital,

• engagement with other services, as required (e.g., smoking cessation service).

#### Baby outcomes are mainly markers of poor perinatal outcome

• composite outcome of adverse perinatal outcome comprising:

- perinatal mortality;

- preterm birth before 34 weeks;

- birth weight 10th centile or below;

- admission to neonatal unit

• Apgar score at 5 minutes,

• arterial *c*ord blood gases, if taken

• breastfeeding initiation rate,

• length of stay in hospital,

• oxygen at 36 weeks post conceptual age, if applicable,

• retinopathy of prematurity, if applicable,

• abnormal cerebral ultrasound prior to discharge (e.g., intraparenchymal cerebral bleed, hydrocephalus, parenchymal cysts), if applicable,

• necrotising enterocolitis (Bells Stage I, II or III), if applicable,

• culture positive sepsis requiring greater than 5 days antibiotic treatment, if applicable.

#### Longer term infant outcomes

• Routine child health assessments, including immunisation uptake and breastfeeding continuation at 6 weeks.

#### Psychological outcomes

• Self efficacy (using Pearlin and Schooler Mastery Scale [17]).

• Mother-to-infant bonding tool [18].

The detrimental impact of maternal bonding difficulties on both the emotional and cognitive development of the child and the quality of the mother-infant relationship has been well documented in the literature [19]. We have therefore chosen to evaluate mother-to-infant bonding.

### Sample size

Currently, NICE recommend, in the Antenatal Care Guideline [20], that the schedule of appointments should be determined by the function of the appointments and for nulliparous women with an uncomplicated pregnancy, they recommend that a schedule of ten visits should be adequate. The actual number of appointments attended was the subject of a survey of women's experiences of maternity care [21] carried out in 2006. This was a national survey which used a random sample of 4800 women and achieved a response rate of 63%. Women were sent a postal questionnaire three months after birth. Nulliparous women reported they attended a mean of 10.9 (standard deviation [SD] 6) antenatal appointments (Table 1).

**Table 1 T1:** Estimated frequency of the events which make up the primary outcomes

Outcome	Average	Source of information
Number of antenatal visits by nullips (consultant and midwife)	Average number of visits 10.9 (SD 6)	Recorded Delivery [21]

Edinburgh Postnatal Depression Scale (EPDS)	Average score5-7 (SD 6)	Psychosocial and psychological interventions for preventing postpartum depression (Cochrane review) [22]

There is some evidence relating to number of antenatal visits and perinatal outcomes. A systematic review [23] found that in settings where the number of visits is already low, reduced visits programmes of antenatal care for low risk women are associated with an increase in perinatal mortality compared to standard care, although admission to neonatal intensive care may be reduced.

An observational study explored the relationship between the number of antenatal visits made by 17,765 British women and adverse perinatal outcomes [24]. No consistent relationship between admission to neonatal unit or perinatal mortality and number of antenatal visits was found. A significant positive relationship was found between number of antenatal visits and Caesarean section, and low birth weight (less than 2500 g) was positively associated with number of visits for nulliparous women but not for parous women. More recently, a cohort study from Finland found under-attending free antenatal care was associated with adverse pregnancy outcomes [25]. Logistic regression analyses found there were significantly more low birthweight infants in the under and non-attenders, with more fetal and neonatal death.

Estimates of the baseline Edinburgh postnatal depression score are taken from the controls of a Cochrane systematic review of Psychosocial and psychological interventions for preventing postpartum depression [22]. It is well documented that a reduction in maternal depression, in addition to improving maternal wellbeing, will have a beneficial effect on short and long term child outcomes and it is plausible that social support provided by the POWs could reduce the numbers of women becoming depressed. Studies have shown that depressed mothers are more likely to demonstrate impaired maternal-infant interactions and negative perceptions of infant behaviour [8]. Children of depressed mothers are more likely to suffer a range of adverse outcomes, including insecure attachment, behavioural problems, cognitive developmental deficits and difficulties in emotional functioning, some of these continuing into adolescence [9,26-29].

A sample size of 421 per arm would provide 90% power (at the 5% significance level) to detect a reduction of 1.5 in the average EPDS score from say 7 to 5.5, and would provide greater than 90% power to detect increased engagement with antenatal services of either 1.5 or 2 visits (Table 2). This calculation has also allowed for 20% drop-out or loss to follow-up.

**Table 2 T2:** Estimated sample size calculations for number of antenatal visits

Average number of antenatal visits	Average number in intervention arm	Difference	Power	Sample sizeper arm
8.9	10.9	2	90%	190

9.4	10.9	1.5	90%	337

Following a successful six month pilot in which 475 women were recruited a revision to the sample size was agreed. Prior to the pilot there was no data on the extent of the social risk factors amongst women and data from the pilot showed that 36% of the women recruited had one social risk factor. It was agreed to power the study to detect the pre-specified differences in the primary outcomes in the sub group of women with two or more social risk factors, which lead to an increase in the sample size to 658 women per arm. It is anticipated that this sample size of 1316 will be obtained by 31st December 2011.

### Statistical analysis

We will calculate the mean number of visits and mean EPDS for each arm and compare differences using the *t*-test or other appropriate non-parametric test. Variations will be explored by pre-specified sub-group comparisons. Variations in participant baseline characteristics between intervention and control groups will also be explored, and if appropriate, variations in participant characteristics adjusted for using generalised linear models with appropriate consideration of strata of randomisation.

For secondary continuous outcomes, variations between control and intervention groups will be investigated using the *t*-test and, if necessary, covariate adjustment made using generalised linear models (to include strata affects); for secondary binary outcomes, differences will be compared using chi-squared tests and, if necessary, logistic regression. For all analyses, assumptions of various tests and models will be explored and non-parametric tests used if required.

All analyses will be by intention to treat and 95% confidence intervals will be quoted throughout. Missing covariate and outcome data will be examined. Reasons for withdrawal, lack of participation and any reasons for non-compliance will be documented and explored. Complete case and available case analyses will be completed in the first instance. If the amount of missing data is not insignificant, then multiple imputation will be used to evaluate sensitivity to the missing completely at random assumption, and inferences compared to those under the lesser missing at random assumption.

Pre-specified sub-group comparisons will be according to number of social risks (1 social risk or 2 or more social risks) identified and gestation at recruitment (< 12 weeks, 12-19 + 6 weeks, 20-27 + 6 weeks). These pre-specified subgroup comparisons will be for the primary outcomes and the more clinically important secondary outcomes (perinatal composite outcome, self-efficacy and Mother-to-infant bonding). The level of significance will at 0.05. The remaining secondary outcomes will have the level of significance at 0.01.

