### Usual care (control)

To maximise access and engagement with maternity services the local PCTs have commissioned a new service model based on social risk assessment, alongside assessing and managing obstetric and medical risk in the usual way. To assess social risk a set of items have recently been included in the standardised maternity notes used universally in Birmingham. These are completed at the booking visit by the midwife and identify whether a woman has any of the following factors:

• UK resident for under a year.

• Difficulty with the English language, both spoken and written.

• Housing problems, such as rent arrears, temporary accommodation, registered with National Asylum Support Service (NASS) or of No Fixed Abode (NFA).

• No support from either partner or family or friend

• Woman/household member in receipt of social services support, including child protection.

• Identified benefit problem.

• Smoking.

• Drug misuse, including other's in the household.

• Alcohol misuse.

• Clinical diagnosis of past or present mental illness.

• Teen parent (under 20 years old).

• Domestic abuse.

• Body Mass Index less than or equal to 18 OR more than or equal to 35.

• Late booking (defined as booking after 18 weeks gestation).

• Did Not Attend 2 or more antenatal appointments (under 28 weeks gestation).

The intention is that systematic social risk assessment will maximise the likelihood that social risk is identified and needs are met. Midwives identifying women with social risk factors currently either signpost women to services that may be beneficial or refer them to specialised agencies or personnel. This may mean they signpost to support agencies (for example, housing or benefit offices) or refer to other agencies (for example, social services), or refer onto the specialist midwives in their Trust. These specialist midwives act as a contact point and provide specific advice and support for women experiencing problems such as domestic abuse, mental health issues or who are teenagers when they are pregnant.

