### Recruitment and randomisation

As part of the booking visit, all women in Birmingham have a systematic social risk assessment undertaken by the midwife. Once social risk has been identified the midwife will offer the support routinely available (as part of standard care) and will discuss the additional support of the POW only available through the trial. If the woman is potentially interested in taking part, her details will be passed to the ELSIPS midwife within the community midwifery team.

Randomisation is by random permuted blocked design stratified by Trust. The randomisation lists were generated by the trial statistician (KH) and then forwarded to the University of Birmingham Primary Care Clinical Research and Trials Unit who provided a telephone randomisation service thus ensuring concealment of allocation.

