Sampling: Initial sampling will be purposive to include two POWs from each of the three localities covered by the service. The rationale behind this was that each locality serves a population with very different socio-demographic characteristics. We will coordinate with the POW managers to ensure that we are able to observe interactions with women at different stages in the POW service. Any further sampling will be theoretical (see analysis below).

Recruitment: Researchers will attend team meetings to inform POWs about the study. Written consent will be obtained from the POWs for the shadowing. If POWs are selected to participate, all their current clients will receive a letter informing them that their POW may be accompanied by a researcher and that they can opt out without it affecting the service they receive. Each POW will confirm orally that the client has received and understood the letter on a case-by-case basis before any meetings are observed.

Analysis: Field notes will be taken during the observation and detailed reflective accounts of the observation written up immediately following the observation. After each day of shadowing, the two researchers will meet to debrief, discuss the data and emerging themes, and to identify additional data required to elaborate the properties of emerging themes and test them. Emergent themes will be used to interrogate existing related theory in the literature and extend it.

Data anonymization and storage: Full field notes will only be available to the core qualitative analysis group (NG, LI, SK). Before dissemination, all data will be anonymized and any potentially identifying features of the clients the POWs worked with will be removed.

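### The primary comparison leaves out Trust, the randomisation stratum, and covariates enter only if the arms look imbalanced; the test stays valid but gives up precision that a pre-specified model would keep

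*Protocol article*

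**What the plan says.** Under Recruitment and randomisation: "Randomisation is by random permuted blocked design stratified by Trust".

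Under Statistical analysis, the primary comparison is introduced with "We will calculate the mean number of visits and mean EPDS for each arm and compare differences using the" and is then named as a t-test or an appropriate non-parametric alternative. No stratum or covariate term is attached to it. Adjustment follows as a second, conditional step, once the arms have been examined for baseline differences: "if appropriate, variations in participant characteristics adjusted for using generalised linear models with appropriate consideration of strata of randomisation". The section names no covariates, gives no criterion for when adjustment is appropriate, and does not say in terms which result is primary.

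Secondary continuous outcomes follow the same pattern, a t-test and then "if necessary, covariate adjustment made using generalised linear models (to include strata affects".

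The same section already uses two baseline factors to define subgroups: number of social risks (one, or two or more) and gestation at recruitment in three bands.

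**The concern.** Two features of the stated rule run against usual practice.

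First, a factor that restricts the randomisation should also appear in the analysis. Stratifying by Trust removes between-Trust variation from the treatment difference, but an unstratified t-test still counts that variation in its standard error. The interval is then wider than it need be.

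Second, adjustment is prompted by observed differences between the arms. Under randomisation these arise by chance. What makes a covariate worth including is how strongly it predicts the outcome, and that can be decided beforehand. A rule that waits for imbalance will usually leave strong predictors out.

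At stake are the precision of both primary results and a clear statement of which model delivers them. The article gives some reason to think Trust matters. It says of the areas served that "each locality serves a population with very different socio-demographic characteristics". Under Setting and population, almost 90% of births in one primary care trust are to women in the most deprived quintile, against about 50% in another. These are service localities rather than the maternity Trusts used as strata, so this is indirect evidence.

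**Working it through.** **Inputs from the article (Sample size, Tables 1 and 2).** Difference 1.5 for each primary outcome; SD 6 for visits and for EPDS; 5% significance, taken as two-sided; 90% power; 20% loss; 36% of pilot women with one risk, so 64% with two or more; 658 per arm.

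**Assumed input.** R², the share of outcome variance explained by Trust or by Trust plus covariates. The article gives none, so a range from 1% to 20% is shown.

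**1. Reproduce the plan's sizes, which contain no stratum or covariate term.**
- n = 2 × (1.960 + 1.282)² × 6² / 1.5² gives 337 per arm, as stated; a difference of 2 gives 190, as stated.
- 337 / 0.80 = 421.25, stated as 421.
- 421 / 0.64 = 657.8, stated as 658.
- Back-check: 658 × 0.64 × 0.80 = 336.9, so about 337 women per arm analysed in the subgroup with two or more risks.

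**2. Size of the unadjusted test when Trust explains R².** The t-test uses the total SD, while the difference truly varies with SD × √(1 − R²). True two-sided size = 2 × [1 − Φ(1.96 / √(1 − R²))].

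**3. Power of the pre-specified model at 337 per arm.** Residual SD = 6 × √(1 − R²); power = Φ(1.5 / (residual SD × √(2/337)) − 1.96).

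| Assumed R² | Size, unadjusted, R² all from Trust | Power, unadjusted, R² all from Trust | Power, pre-specified model | 95% CI half-width, pre-specified | n per arm for 90% |
|---|---|---|---|---|---|
| 0 | 0.050 | 90.1% | 90.1% | 0.906 | 337 |
| 1% | 0.049 | 90.2% | 90.4% | 0.901 | 333 |
| 2% | 0.048 | 90.3% | 90.6% | 0.897 | 330 |
| 5% | 0.044 | 90.6% | 91.5% | 0.883 | 320 |
| 10% | 0.039 | 91.2% | 92.8% | 0.859 | 303 |
| 20% | 0.028 | 92.5% | 95.2% | 0.810 | 269 |

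The unadjusted half-width is 0.906 in every row. Leaving out Trust alone costs 90.4 − 90.2 = 0.2 points at R² 1% and 92.8 − 91.2 = 1.6 points at 10%. Where R² comes from covariates that were not stratified on, the unadjusted test stays at 90.1%, so the gain is 92.8 − 90.1 = 2.7 points at 10% and 95.2 − 90.1 = 5.1 points at 20%.

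**4. What the imbalance trigger recovers.** Simulation with 337 per arm and five independent covariates each explaining 4% (20% in all), adjusting only for those with a baseline |z| above 1.96; 20,000 null trials and 8,000 with a difference of 1.5.

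| Analysis | Rejection under the null | Power |
|---|---|---|
| Unadjusted | 5.3% | 90.0% |
| Imbalance-triggered | 4.6% | 90.8% |
| Pre-specified, all five | 4.8% | 94.8% |

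The trigger recovers 90.8 − 90.0 = 0.8 points of an available 94.8 − 90.0 = 4.8.

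**5. All randomised women.** 658 × 0.80 = 526 analysed per arm gives 98.2% power unadjusted. There the benefit is mainly a narrower interval.

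**The case against.** The strongest defence is that nothing here threatens validity and the trial reaches its planned power without adjustment. That stands. The sample sizes were derived for an unadjusted comparison and they reproduce.

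Four stronger readings are tempting, and the article does not support them.

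- *The plan ignores the stratification.* It does not. Strata are mentioned for both the primary and the secondary continuous outcomes, but only within the conditional model.
- *Letting imbalance choose the model inflates false positives.* The simulation shows no such inflation (4.6% under the null). A rate of about 7.1% appears, at R² 20%, only if an analyst may claim success on either the unadjusted or the fully adjusted result. The article does not propose that, and the order of its text suggests that the t-test is the main comparison.
- *Precision equal to 11% or 25% more women is being lost.* Those figures are 1/(1 − 0.10) and 1/(1 − 0.20). They rest entirely on an assumed R² of 10% or 20% from baseline factors.
- *Visits attended before randomisation are already recorded, so they can be adjusted for at once.* The article does not say so. The only attendance item in the risk list concerns missed appointments.

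A further objection is that covariate lists belong in an analysis plan, which is not shown. That is fair for the details, and their absence is not the criticism. The article does not leave the matter open, however: it states a rule in which observed baseline differences prompt adjustment, and that rule can be judged as written.

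**Conclusion.** The point holds as one of efficiency and clarity. The plan stratifies by Trust, then compares the primary outcomes without it, and lets covariates in only after baseline differences have been examined.

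For Trust alone the effect is conservative and probably small: size about 0.048 to 0.039 for an assumed R² of 2% to 10%, and a loss of about 0.2 to 1.6 power points for an assumed R² of 1% to 10%. For prognostic factors more generally, the trigger forgoes most of whatever gain exists. Power at 337 per arm would be about 91.5%, 92.8% or 95.2% for an assumed R² of 5%, 10% or 20%, against 90.1% unadjusted.

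The structure of the rule is certain from the text; the size of the loss is not, because it depends on an R² that the article does not give. The change is worth making because it costs almost nothing, not because the planned test would mislead.

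**What to change.** For each primary outcome, state that the primary analysis is a linear model for the difference in means, with Trust as a fixed effect plus number of social risks and gestation at recruitment, fitted whatever the baseline table shows. Enter the number of risks as a count, since the two-level grouping is constant within the subgroup with two or more. Delete the imbalance-triggered rule and keep the unadjusted t-test as a sensitivity analysis.

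Two further covariates are conditional:
- Visits attended before randomisation, for the visits outcome, only if that count is confirmed to be collected.
- The item "Clinical diagnosis of past or present mental illness", for EPDS, only with allowance for its overlap with the risk count, since it is one of the listed risks (Usual care).

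The cost is wording in the analysis section, a check on which baseline items are held, and a stated way of handling missing covariate values. Recruitment and sample size do not change, and the target remains a difference in means. If a separate analysis plan already fixes such a model, the two documents need only be aligned.

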### Outcome measures

The primary outcomes have been chosen on the basis that they are linked to maternal and infant health. The two primary outcomes are engagement with antenatal care, assessed based on number of antenatal visits, and maternal depression, assessed using the Edinburgh Postnatal Depression Scale [16] (EPDS) at 8-12 weeks after birth.

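### The missing-data plan for EPDS stops at missing at random and makes imputation depend on an undefined trigger, so it cannot show whether the result withstands non-response that differs by arm

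*Protocol article*

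**What the plan says.** One of the two primary outcomes is the "Edinburgh Postnatal Depression Scale [16] (EPDS) at 8-12 weeks after birth" (Outcome measures). Arm means are compared by a t-test or a non-parametric alternative (Statistical analysis).

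The same section sets the order for missing data. It starts with: "Complete case and available case analyses will be completed in the first instance". Then: "If the amount of missing data is not insignificant, then multiple imputation will be used". The stated purpose of the imputation is to test sensitivity to MCAR by comparing inferences with those under MAR. No weaker assumption is named. The section also promises to examine missing data and to record and explore reasons for withdrawal and non-participation, but it attaches no analysis to that.

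On the amount of loss, the Sample size section says: "This calculation has also allowed for 20% drop-out or loss to follow-up".

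**The concern.** Two features of the trial make informative non-response to EPDS plausible.

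- The outcome is itself a depression score, and the social risk items that make women eligible (Usual care) include mental illness and missed appointments. Whether a woman provides an EPDS may depend on how she would have scored.
- The Pregnancy Outreach Worker (POW) service aims to raise engagement, and its contact runs to 6 weeks after birth (Intervention). EPDS is measured 2 to 6 weeks after that. Only one arm has this contact, so it may change how many women respond, or which ones.

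If non-responders differ from responders in a way that recorded covariates do not capture, and the pattern differs by arm, the complete-case and MAR results can agree with each other and both be wrong. An apparent benefit could partly reflect who answered. A null result could arise because POWs kept depressed women in follow-up. Comparing MCAR with MAR does not address either possibility.

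**Working it through.** **Inputs from the Sample size section.** Target difference 1.5 EPDS points; SD 6 (Table 1); 5% significance (taken as two-sided) and 90% power; 20% loss; 36% of pilot women with one risk factor, so 64% with two or more; 658 per arm after revision.

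**Reproducing the plan's figures.**
- Evaluable per arm: 2 × (1.960 + 1.282)² × 6² / 1.5² = 336.2, so 337.
- With 20% loss: 337 / 0.80 = 421.25 (stated: 421).
- For the subgroup with two or more risks: 421 / 0.64 = 657.8 (stated: 658).

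**What 20% loss means at 658 per arm.** 0.20 × 658 = 131.6, about 132 women per arm without EPDS. That leaves 0.80 × 658 = 526.4 per arm, of whom 0.64 × 526.4 = 336.9 are in the subgroup. Power for 1.5 points is then 98.2% overall and 90.1% in the subgroup. The allowance protects precision; it does nothing about bias.

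**Bias identity.** Let p be the proportion missing in an arm, and d the mean EPDS of its non-responders minus that of its responders (T = intervention, C = control). For the difference T − C:

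full-sample difference − observed difference = pT·dT − pC·dC

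The documents give no value for d and no loss by arm, so the values below are assumptions. The observed difference is set at −1.5.

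| Loss T / C | dT / dC | Bias term | Full-sample difference |
|---|---|---|---|
| 20% / 20% | 3 / 3 | 0 | −1.5 |
| 20% / 20% | 3 / 0 | +0.6 | −0.9 |
| 20% / 20% | 0 / 3 | −0.6 | −2.1 |
| 20% / 20% | 6 / 0 | +1.2 | −0.3 |
| 25% / 15% | 3 / 3 | +0.3 | −1.2 |
| 15% / 25% | 3 / 3 | −0.3 | −1.8 |

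A 3-point departure in one arm at 20% loss moves the estimate by 0.6 points, which is 0.6 / 1.5 = 40% of the target difference.

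**Tipping points.** With 20% loss in each arm, only dT − dC matters. The 95% confidence interval reaches zero when 0.20 × (dT − dC) = 1.5 − half-width.
- Two or more risks: half-width 1.96 × 6 × √(2/336.9) = 0.906; shift (1.5 − 0.906) / 0.20 = 2.97, about 3.0 points or half an SD.
- All women: half-width 1.96 × 6 × √(2/526.4) = 0.725; shift (1.5 − 0.725) / 0.20 = 3.88, about 3.9 points.
- The point estimate itself reaches zero at 1.5 / 0.20 = 7.5 points.

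These figures keep the standard error at its observed-data value and take the MAR estimate to equal the observed one. If covariates move the MAR estimate, the starting point moves with it.

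**The case against.** The strongest reply is that this is a condensed article. A numeric trigger, the imputation model and a missing-not-at-random (MNAR) analysis may sit in an analysis plan that is not shown, and the article does not rule them out. That holds for the imputation detail, which is not criticised here. It does not fully answer the point, because the article itself states the order of analyses, the condition for imputation and the assumption at which sensitivity work ends.

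Other parts of the defence stand:

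- At 20% loss most readers would regard the trigger as met, so the vague condition alone does little harm.
- EPDS is measured once and no baseline EPDS is described. Imputation from baseline covariates may therefore add little to an adjusted analysis of observed women. Which of them is the main analysis is a matter of preference.
- For an unadjusted comparison of a single score, complete case and available case analyses largely coincide.
- Analysing observed outcomes as randomised and calling it intention to treat is common usage. It is not a contradiction.
- Examining missing data, if done by arm, would show different response rates. Only the part that depends on the unseen score stays hidden. No analysis can detect that part; a delta analysis shows only how far a conclusion depends on it.

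**Conclusion.** The point holds as a cheap improvement. The planned comparison of MCAR with MAR cannot show whether an EPDS conclusion withstands arm-specific informative non-response, and the trial's design makes that form of non-response plausible. Under the assumptions of 20% loss in each arm, an observed difference of 1.5 and SD 6, the interval reaches zero at a relative shift of about 3.0 points (two or more risks) or 3.9 points (all women).

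A reader might infer more than the documents support:

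- **That one woman in five is expected to lack EPDS.** The 20% is a sample-size allowance for drop-out or loss, not a forecast of EPDS non-response.
- **That the planned analysis favours the intervention.** The direction is unknown. Equal loss with an equal shift gives no bias. If POW contact improved response (15% against 25% loss, 3-point shift in both arms), the observed result would understate the benefit.
- **That depressed women will fail to respond.** This is a plausible inference which the article neither states nor excludes. The shifts and the unequal loss rates used above are assumptions.
- **That the observed-data comparison must be replaced as the main analysis.** Nothing here requires that.

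**What to change.** 1. Keep the observed-data comparison of EPDS as the main analysis, if preferred.
2. Run the MAR multiple imputation for EPDS whatever the amount missing, and drop the undefined trigger.
3. Pre-specify an MNAR sensitivity analysis that shifts the imputed EPDS values by 0 to +6 points, separately in each arm, and report the tipping point. Six points is one SD on the plan's own figure, and the range contains both confidence-interval tipping points above.

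This needs no new data and no change to the sample size. The cost is a little more analysis work, and the possibility that the conclusion is shown to be sensitive to non-response.
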